### Primary hypothesis

The DREAMS initiative will collectively reduce HIV incidence amongst AGYW by 25% by the end of year one of its implementation, and by 40% by the end of year two in those districts where DREAMS programmes were implemented.

### Study aim

The aim of this study is to determine the impact of the DREAMS initiative on HIV incidence amongst a household-based representative sample of AGYW (12–24 years) in four of the five districts in KwaZulu-Natal (KZN) and Gauteng (GP), South Africa. An HIV incidence baseline will be estimated primarily using incidence findings from existing studies. HIV incidence in the South African National HIV Prevalence, Incidence, Behaviour and Communication Survey Study (SABSSM) used a similar incidence bio-marker-based methodology to one adopted for this study. The HIV incidence findings for AGYW 15–24 years at the national level was 2.54% (95% CI 2.04–3.04) in 2012. An earlier longitudinal study on HIV uninfected 14–30 year old women, undertaken between March 2004 and May 2007, revealed that HIV incidence in young girls below the age of 18 years was 4.7 [95% Confidence interval (CI) 1.5–10.9) compared to 6.9 (95% CI 4.8–9.6)/100 women years (wy) in those aged 18 - 30 [32]. The HIV Incidence Provincial Surveillance System (HIPSS) situated in uMgungundlovu, KZN, included two cross-sectional surveys between June 2014 and June 2015 and between July 2015 and July 2016. The HIPSS study population was drawn from uMgungundlovu, the same area for this study. The HIPSS incidence in adolescent girls 15–19 years was 4.63% (95%CI, 3.29–6.52) and 4.00% (95% CI, 2.74–5.85) for women 20–24 years old in the 2014 survey [33].

### Study objectives

The primary objective of this study is:
Measure the change in HIV-1 incidence following implementation of the DREAMS suite of interventions within a ‘real world, non-trial setting’.

The secondary objectives are to:
Measure HIV prevalence, and proportion of HIV positive AGYW on ART and ART naïve with detectable and undetectable HIV-1 Ribonucleic Acid (RNA) viral load.Measure prevalence of pregnancies and sexually transmitted infections (STIs) including Hepatitis B virus (HBV), Herpes simplex virus type 2 (HSV-2), syphilis, human papillomavirus (HPV*), Chlamydia trachomatis*, *Neisseriae gonorrhoea*, *Trichomonas vaginalis* and *Mycloplasma genitalium.*Measure risky sexual behaviour, specifically, the number of past year sexual partners, condom use, and age-disparate and concurrent partnering.Measure the prevalence of intimate partner violence.Measure performance on selected academic milestones (e.g. academic progress, school completion rates).Measure the economic empowerment of AGYW, socio-economic status of their family and selected parent/guardian/caregiver indicators.To measure the exposure to the DREAMS programme including condom promotion and provision (male and female); HIV testing services (HTS) and linkage to care; GBV prevention and post violence care and support; comprehensive sexual reproductive health rights (SRHR) services; social asset building interventions; school-based HIV and violence prevention; community mobilization and norms change; parenting/caregiver programmes.

## Methods/design

### Study setting

The four study districts (City of Johannesburg, Ekurhuleni, uMgungundlovu and eThekwini) consist of an estimated 12,073,421 individuals. uMkhanyakude, the fifth DREAMS district, is not part of this evaluation.

The province of KZN remains the worst affected by HIV with an overall prevalence of 15% amongst 15 to 49 year old inhabitants in 2015 [34]. The two districts of interest within KZN, uMgungundlovu (20% HIV prevalence in 2016) and eThekwini (16.8% HIV prevalence in 2016) are among those with the highest HIV prevalence in South Africa [34]. eThekwini contains the third-largest city in the country (Durban), which is the busiest port on the African continent and the main economic hub within the province of KZN [35]. About 68% of eThekwini is considered rural and 32% urban.

uMgungundlovu is the second largest district in KZN after eThekwini and is located in central KZN. uMgungundlovu includes traditional settlements or farmlands, informal, rural and urban settlements. Its local municipalities are largely rural, while the Msunduzi Municipality is highly industrialized. The largest city within the uMgungundlovu district is Pietermaritzburg, which is also the capital of KZN.

The Gauteng province (GP), whilst geographically the smallest, is the most populous province in South Africa. GP has the fifth highest provincial HIV prevalence in the country with a prevalence of 11.1% in 2016 [34]. The HIV prevalence in the two study districts, City of Johannesburg and Ekurhuleni is 11.1 and 14.3% respectively [8]. These districts are densely populated. Whilst highly urbanised with a diverse economy, large urban townships including Katlehong and Tokoza which form part of the Ekurhuleni district. The HIV prevalence amongst AGYW in the City of Johannesburg and Ekurhuleni was estimated to be is 3% in 2012 [36].

### Study design

This study is a single cross-sectional survey targeting 18,500 AGYW, to be conducted in 2017/2018 in four selected districts in South Africa. AGYW between 12 and 24 years will be selected using a stratified cluster-based sampling approach, with districts representing strata and the cluster or primary sampling unit being the small area layers (SALs). SALs were created by merging adjacent Enumeration Areas (EA), which had less than 500 people, to create a spatial area layer that corresponded as closely as possible to the EA layer. The following criteria were used for the establishment of the SALs. EAs were merged if they fell within the same sub-place (a higher order geographic level); EAs were merged if they had the same geographical properties; an EA was merged if its population that resided there was less than 500 people; and lastly, the resulting SALs must have a population total of 500 or more [37].

Stratified sampling was chosen as it reduces sampling error and ensures a greater level of representation when compared to simple random sampling [38]. It also ensures more precise estimates, provided that there is homogeneity within strata and heterogeneity between strata [38]. A questionnaire will be administered and biological samples collected (two micro-containers of blood for dried blood spot (DBS), plasma specimens and self-collected vulvo-vaginal swab samples (VVSS) to test for HIV infection, HIV incidence, STIs as well as pregnancy respectively).

Additionally**,** we will conduct 64 focus groups discussions (FGDs). Thirty two in one district in GP (city of Johannesburg) and thirty two in one district in KZN (uMgungundlovu). The districts were randomly selected. Individuals exposed to DREAMS interventions will be recruited to participate in the study. The FGDs in each district will include: 1) adolescent girls 16 to 18 years old (*n* = 8), 2) adolescent girls and young women 19 to 24 years old (*n* = 8) 3) young men aged from 25 to 35 years old (*n* = 8), 4) stakeholders who support adolescent girls and young women such as teachers, nurses and police men (*n* = 4) and 5) DREAMS implementation partners (*n* = 4). This qualitative component will provide additional insight into the impact of DREAMS interventions on AGYW in relation to the study objectives whilst also identifying facilitators and barriers to accessing the DREAMS interventions. The study followed the Strengthening the Reporting of Observational Studies in Epidemiology (STROBE) guidelines (See Additional file 1).

### Study population

According to 2011 census data [39] the four study districts consist of an estimated 3,679,700 households containing approximately 1,633,906 AGYW. Additional characteristics of the population within the selected districts are listed in Table 1.

**Table 1 Tab1:** Characteristics of the population within SA DREAMS IE districts (2011–2017)

	eThekwini	uMgungundlovu	City of Johannesburg	Ekurhuleni
Population Size: 10–24 years AGYW [39]	500,214	153,722	584,104	395,866
Population density per square km [39]	1501.90	113.90	2695.90	1652.00
HIV ANC Prevalence (%) [40]	41.1	42.5	27.5	33.5
People living with HIV (PLHIV) [8]	516,167	225,284	533,960	468,521
Number of AGYW 10–19 years receiving grants^a^ [41]	64,716	84,942	189,845	155,135
Number of Orphans [41]	86,734	42,000	61,634	55,261
Number of Girls in schools Ages 10–20 years [42]	238,544	74,602	276,185	161,182
Teenage pregnancy (deliveries at facility in women under 18 yrs. and not terminations) (%) [31]	7.0	8.5	3.6	6.2
Number of SALs	300	150	300	300
Number of households	956,713	272,666	1,434,856	1,015,465

Notes: ^a^In this context, a grant refers to the social assistance provided by the South African Social Security Agency in the form of different grants for children (for example Foster Child Grant, Care Dependency Grant, Child Support grant and Grant-in-aid)

### Sampling strategy

A stratified cluster-based sampling design has been adopted, specifically:
The four districts will be considered as the primary strata.In order to reach 18,500 AGYW in each survey, a total of 1050 SALs will be selected and distributed between KZN and GP, proportional to the targeted sample size in each province (i.e. 10,500 AGYW in GP and 8000 in KZN), resulting in 450 SALs for KZN and 600 for Gauteng. A total of 300 SALs will be selected from eThekwini and 150 from uMgungundlovu; 300 from the City of Johannesburg and 300 from Ekurhuleni, this is proportional to the population size of the districts. uMgungundlovu is less than one third the size of eThekwini, however to ensure that estimates are reported with a higher level of precision for uMgungundlovu SALs were allocated in the ratio of 2:1 between uMgungunglovu and eThekwini.To achieve a minimum of 18 AGYW per SAL, taking into account that approximately 1 in 2 households have an eligible individual, and a non-response rate of 20%, 55 households will be randomly chosen within each SAL in order to attain a household-representative sample of AGYW [43].All eligible AGYW in the household will be approached for inclusion in the study.

The SAL sampling frame has been triangulated using 2011 census data [39], the 2007 Community survey data [38] and aerial imaging to determine the number of households and population estimate at the SAL level. The SAL sampling frame will be checked across these three data sources and estimates calculated according to province and district boundaries, whilst the population will be further classified according to race, gender and age. To adjust for unequal probability of selected SALs, non-response and to facilitate the interpretation of results at the provincial level, sampling weights will be used in all analyses. From a total of 19,366 SALs across the study area, approximately 1050 SALs will be selected to reach the targeted sample size. The sample size is based on the required number of AGYW (i.e 18,500) and working upwards to determine how many households need to be approached to realise this sample size. If one in two households have an AGYW [39], to obtain 18,500 we would need to approach 37,000 households (assuming they all agree to participate). However, we anticipate that 20% of households will not agree to participate and about 12.5% are unoccupied or invalid (so anticipate approaching 55,000 households).

Study staff will identify households using a Global Positioning Systems receiver to record the geographic coordinates of each randomly selected household. Fieldworkers will visit approximately 55 households from each SAL. Recruitment will continue until the required number of study participants are enrolled. Should a selected household be abandoned, refuse to complete the composition form or should the members be away for an extended period, the next household on the sampling frame will be approached.

The required number of SALs for the evaluation will be randomly selected. Sufficient oversampling of households will be done to avoid repeated sampling of households.

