### Statistical considerations and sample size calculation

The sample size of 8000 per survey in the two KZN districts will have 80% power to detect a reduction of 40% in the HIV incidence rate at the 5% significance level given a false recent rate (FRR) of 0.01%, HIV prevalence of 25%, and an initial HIV incidence rate of 4 per 100 person years (py) [33]. A sample size of 10,500 per survey in the two GP districts will have 80% power to detect a 40% reduction in HIV incidence given a FRR of 0.01%, HIV prevalence of 25% and baseline incidence of 3/100py amongst AGYW aged between 12 and 24 years [8].

The aforementioned sample size calculations are based on detecting change in incidence and not the precision of individual estimates. However, the sample size of 8000 in KZN is adequate to estimate an HIV incidence rate of 4% with a coefficient of variation of 12%, corresponding to a confidence interval of (3.1–4.9%). The sample size in Gauteng of 10,500 will allow us to estimate the HIV incidence rate of 3% with a coefficient of variation of 12% and confidence interval of (2.28–3.72).

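### The one-in-two household assumption contradicts the protocol's own census figures (0.40 AGYW per household in Gauteng), so the planned 55 households per SAL understate the Gauteng fieldwork

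*Protocol article*

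**What the plan says.** All of the following is in the protocol article.

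- Sampling strategy, on the number per cluster: "To achieve a minimum of 18 AGYW per SAL", and then "approximately 1 in 2 households have an eligible individual, and a non-response rate of 20%, 55 households will be randomly chosen within each SAL". All eligible AGYW in a household are approached.
- Sampling strategy, on the total: "If one in two households have an AGYW [39], to obtain 18,500 we would need to approach 37,000 households". The reference given is the census. On losses: "we anticipate that 20% of households will not agree to participate and about 12.5% are unoccupied or invalid", which leads to a stated 55,000 households to be approached.
- Sampling strategy, on allocation: 600 SALs in Gauteng for 10,500 AGYW and 450 in KwaZulu-Natal for 8,000.
- Sampling strategy, closing paragraphs: about 55 households are visited per SAL. A household that is abandoned, refuses or is away for long is replaced by the next one on the frame, and enrolment goes on until the required number is reached.
- Study population, from the 2011 census: "the four study districts consist of an estimated 3,679,700 households containing approximately 1,633,906 AGYW". Table 1 splits both totals by district; its AGYW row covers ages 10–24.
- Eligibility criteria: females aged 12–24.
- Statistical considerations: "A sample size of 10,500 per survey in the two GP districts will have 80% power", and a coefficient of variation of 12% is attached to the same 10,500.

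**The concern.** The household count depends on one planning ratio, and the ratio is attributed to the same census that supplies the population figures. The share of households with at least one AGYW can never exceed the mean number of AGYW per household. A mean of 0.444 overall, or 0.400 in Gauteng, therefore rules out one household in two. Since every eligible AGYW in a household is approached, AGYW per household is also the correct yield.

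One fixed number of households per SAL is used everywhere, although Gauteng has the larger target and the lower yield. If the visits are budgeted at 55 per SAL, the 10,500 behind Gauteng's stated power and precision has to come from more households than the plan counts. The protocol does not say how many.

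**Working it through.** **Inputs.** Table 1, AGYW 10–24 and households: eThekwini 500,214 and 956,713; uMgungundlovu 153,722 and 272,666; Johannesburg 584,104 and 1,434,856; Ekurhuleni 395,866 and 1,015,465. They sum to 1,633,906 and 3,679,700, exactly the Study population totals, so numerator and denominator belong together. Sampling strategy: 55 households per SAL, 20% refusal, 12.5% unoccupied or invalid. Assumption, not in the documents: 13/15 = 0.867 of the 10–24 group are aged 12–24 (even spread over single years), with 0.84 to 1.00 as the range.

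**The plan's own figures.** 18,500 / 0.5 = 37,000. With the two losses added, 37,000 / (1 − 0.20 − 0.125) = 54,815, which reproduces the stated 55,000. Per SAL, 55 × 0.5 × 0.8 × 0.875 = 19.3 (18.6 with additive losses), so at least 18 follows if 0.5 is right. The arithmetic is sound; the ratio put into it is not.

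**AGYW per household from Table 1.**

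| District | Ages 10–24 | Ages 12–24 (× 13/15) |
|---|---|---|
| eThekwini | 0.523 | 0.453 |
| uMgungundlovu | 0.564 | 0.489 |
| Johannesburg | 0.407 | 0.353 |
| Ekurhuleni | 0.390 | 0.338 |
| Gauteng (979,970 / 2,450,321) | 0.400 | 0.347 |
| All four | 0.444 | – |

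**Gauteng yield.** Formula: SALs × households per SAL × AGYW per household × 0.8 × 0.875. The planned households are 600 × 55 = 33,000.

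- Ratio needed for 10,500: 10,500 / (33,000 × 0.7) = 0.455. Both Gauteng districts lie below it, even on the 10–24 count.
- All 10–24 counted as eligible: 33,000 × 0.39994 × 0.7 = 9,239, which is 12% below target (8,909 with additive losses).
- 13/15 eligible: 9,239 × 13/15 = 8,007, which is 24% below (7,721 with additive losses).
- 0.84 eligible: 7,760, which is 26% below.
- Weighting the two districts by their equal 300 SALs instead of pooling gives 9,204 and 7,977, so pooling makes no material difference.

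**KwaZulu-Natal yield.** 55 × (300 × 0.453 + 150 × 0.489) × 0.7 = about 8,055 with the 13/15 share (7,808 with 0.84), against 8,000.

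**Gauteng households needed.** The target per SAL is 10,500 / 600 = 17.5. Then 17.5 / (0.400 × 0.7) = 62.5, about 63 on the 10–24 count, and 17.5 / (0.347 × 0.7) = about 72 with the 13/15 share.

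**Approached or completed.** 1,050 × 55 = 57,750, close to the 55,000 to be approached. On that reading, 55 counts approaches and the losses are already inside it. If instead every lost household were replaced so that 55 were completed per SAL, Gauteng would yield 33,000 × 0.347 = about 11,440 AGYW aged 12–24 before individual refusals. The total to be approached would then be 57,750 / 0.7 = 82,500, not 55,000.

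**The case against.** The strongest reply is the replacement rule. Refusing, abandoned and long-absent households are replaced and recruitment continues to target, so most of the losses deducted above need not be permanent. With full replacement, Gauteng would exceed 10,500. This stands as far as the final sample size goes. It does not rescue the household counts, because full replacement means about 82,500 approaches against the 55,000 stated.

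Second, the sentence that sets 55 names only the 20% non-response. With that loss alone and 0.40 AGYW per household, 33,000 × 0.40 × 0.8 gives 10,558, which meets the target. But this needs both the omission of the 12.5% that the same section states and the counting of girls aged 10–11. With 20% alone and the 13/15 share, the figure is 9,151.

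Third, the 13/15 share is not documented. True, so about 8,000 is conditional on it. The 9,239 does not use it and is still short.

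Fourth, the wording is only approximate, and Table 1 carries dates from 2011 to 2017, so household numbers at the time of the survey may differ. That is fair for the exact size. The protocol nevertheless cites the census for its ratio, and the census figures it prints do not give that ratio.

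**Conclusion.** The assumption that half of households hold an eligible AGYW is wrong on the protocol's own figures, overall and most clearly in Gauteng. With both stated losses and no replacement, the planned 33,000 Gauteng visits yield about 7,800 to 9,200 AGYW against 10,500. That is 12% to 26% short for age shares from 1.00 down to 0.84. Individual refusal and parental consent for minors come on top of household refusal and would lower the yield further; the documents give no rate for them. KwaZulu-Natal is about on target, so the problem is a Gauteng one.

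A reader might infer that Gauteng will miss its sample size and lose its stated 80% power. The documents do not support that. Recruitment runs until the number is reached, so the final sample is not fixed by the 33,000 visits. The mean duration of recent infection, which a power recalculation would need, is not given either. What is established is that the Gauteng workload is understated and that 55 per SAL and 55,000 in total do not fit the replacement rule. The 55,000 itself is computed correctly from its inputs.

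**What to change.** 1. Replace the one-in-two ratio with eligible AGYW aged 12–24 per household for each district, taken from the census by single year of age, so that no age assumption is needed.
2. Then choose one of two routes. Either restate the Gauteng households per SAL (about 63 on the 10–24 count, about 72 with the 13/15 share) and the total to be approached; or keep 55, state the expected Gauteng number, and recompute power and coefficient of variation for it from the inputs used for the stated values.
3. Say whether 55 counts households approached or completed, and bring the count, the total and the replacement rule into agreement.

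The restatement and the clarification cost only a few lines of text. Issuing more households is the only real expense: 600 × 63 = 37,800 or 600 × 72 = 43,200 Gauteng visits instead of 33,000.

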### Eligibility criteria

All females aged 12–24 years residing in sampled households and who are willing to participate in this cross-sectional study and undergo the study procedures including an HIV test, will be included in the study. People who do not speak English, Zulu, Sotho, Afrikaans, who have cognitive or mental challenges (based on the assessment of the participant’s ability to comprehend the study information provided) and those who are deaf and/or mute will be excluded from the study. Individuals in institutions (hostels, prisons and hospitals) will not be eligible for participation in the study.

### Statistical considerations and sample size calculation

The sample size of 8000 per survey in the two KZN districts will have 80% power to detect a reduction of 40% in the HIV incidence rate at the 5% significance level given a false recent rate (FRR) of 0.01%, HIV prevalence of 25%, and an initial HIV incidence rate of 4 per 100 person years (py) [33]. A sample size of 10,500 per survey in the two GP districts will have 80% power to detect a 40% reduction in HIV incidence given a FRR of 0.01%, HIV prevalence of 25% and baseline incidence of 3/100py amongst AGYW aged between 12 and 24 years [8].

The aforementioned sample size calculations are based on detecting change in incidence and not the precision of individual estimates. However, the sample size of 8000 in KZN is adequate to estimate an HIV incidence rate of 4% with a coefficient of variation of 12%, corresponding to a confidence interval of (3.1–4.9%). The sample size in Gauteng of 10,500 will allow us to estimate the HIV incidence rate of 3% with a coefficient of variation of 12% and confidence interval of (2.28–3.72).

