## Discussion

Ending the HIV/AIDS pandemic by 2030 requires the continual monitoring and evaluation of prevention programmes, with the aim of optimising efforts and ensuring the achievement of epidemic control. The monitoring of HIV prevalence is largely done through household surveys in SA [8]. However, key to determining the impact of initiatives targeting high-risk populations, including AGYW, is the collection of detailed data on the HIV response in a real world context, linking the scale-up of prevention efforts to changes in HIV incidence at a population level. This study will determine the impact DREAMS interventions have had on HIV incidence among AGYW in a ‘real world, non-trial setting’. This will be done by measuring HIV transmission within high-prevalence settings and within a high-risk population group, which will provide insights into the impact and efficacy of the DREAMS suite of prevention interventions.

The monitoring of temporal trends of HIV indicators will assist in improving and targeting prevention efforts and planning for health care delivery needs. This evaluation will be useful in implementing broader surveillance strategies and ensure they are supportive of the DREAMS interventions most effective to reduce risky sexual behaviour, increase knowledge of HIV status and subsequent uptake of ART, as well as reduce the prevalence of GBV.

This study has some limitations. Baseline incidence will need to be estimated. A longitudinal study design would have been preferred to establish baseline incidence prior to commencement of the DREAMS interventions and within the DREAMS targeted areas. Furthermore, a cross-sectional study cannot measure changes in behaviour and HIV incidence over time. This study would also not be able to determine the long-term impact of DREAMS being limited to information based on data gathered at a specific point in time. The study will only select participants from DREAMS targeted areas with the change in HIV infection rates estimated following the implementation of DREAMS programmes amongst AGYW through computation of the population’s attributable risk. As there is no non-DREAMS comparison arm in the study design, causal inferences regarding the relative contribution of DREAMS activities to measured reductions in key parameters is limited. The nature of the study did not allow for the establishment of a control group to assess the relative impact of the DREAMS interventions.

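### The stated 80% power belongs to two own surveys per province, but the plan runs one survey against a baseline estimated from other studies

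*Protocol article*

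**What the plan says.** All places are in the protocol article.

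- **Statistical considerations and sample size calculation.** For KZN: "The sample size of 8000 per survey in the two KZN districts will have 80% power to detect a reduction of 40" per cent. The inputs behind this figure read "at the 5% significance level given a false recent rate (FRR) of 0.01%, HIV prevalence of 25%, and an initial HIV incidence rate of 4", in units of 100 person-years. For GP: "A sample size of 10,500 per survey in the two GP districts will have 80% power to detect a 40% reduction in HIV incidence". The starting rate there is a "baseline incidence of 3/100py amongst AGYW aged between 12 and 24 years". The section adds that these sizes rest on detecting change, and that one survey alone would estimate incidence with a coefficient of variation (CV) of 12% in each province.
- **Sampling strategy.** The target of 18,500 is also worded as applying to each of several surveys.
- **Study design.** "This study is a single cross-sectional survey targeting 18,500 AGYW", in 2017/2018.
- **Study aim.** "An HIV incidence baseline will be estimated primarily using incidence findings from existing studies". Recent figures quoted with intervals are a national estimate for ages 15–24 in 2012, 2.54% (2.04–3.04), and the HIPSS estimates from uMgungundlovu, 4.63% (3.29–6.52) at ages 15–19 and 4.00% (2.74–5.85) at ages 20–24.
- **Primary hypothesis.** DREAMS "will collectively reduce HIV incidence amongst AGYW by 25% by the end of year one of its implementation". A second clause sets a 40% target for year two. **Outcomes and analysis** then asks only whether the 40% at two years was achieved.
- **Discussion.** Baseline incidence has to be estimated, and "a cross-sectional study cannot measure changes in behaviour and HIV incidence over time".

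**The concern.** The primary objective is a change in incidence, and the only power statement for it assumes a second survey of the same size that the design does not contain. In the planned comparison, the first half of the contrast is an external estimate with its own sampling error, from a population that only partly overlaps the surveyed one. The power then depends on that external error, which the sample size section does not use.

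At stake is how the main result is read. A non-significant change would be taken as coming from a design with 80% power for a 40% fall, and a significant one as a confirmed reduction, although neither reading has been shown to fit the comparison that will be made. Two further parts of the primary question have the same root. A single survey in 2017/2018 gives no separate year-one measurement, so the 25% clause cannot be tested. And asking whether 40% was achieved differs from testing for no change, which is what the power figure addresses: if the true reduction is exactly 40%, the estimate falls short of 40% about half the time.

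**Working it through.** **Inputs from the article.** N = 8,000 (KZN) and 10,500 (GP); prevalence P = 0.25; false recent rate ε = 0.0001; incidence 4 to 2.4 (KZN) and 3 to 1.8 (GP) per 100 person-years; 5% level, taken as two-sided.

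**Assumed, because the article does not give them.** MDRI 118–130 days; design effect (DEFF) 1 unless stated. Leaving these out of a condensed article is not counted as a fault.

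**Formulas.** With m = MDRI/365.25 and R = [I(1−P)(m−ε) + εP]/P:
- expected recent infections = N·P·R
- CV² = DEFF × (1/(N·P)) × [1/(1−P) + R(1−R)/(R−ε)²]
- power, difference scale = Φ{(I₁−I₂)/√[(I₁CV₁)² + (I₂CV₂)²] − 1.96}
- power, log scale = Φ{ln(I₁/I₂)/√(CV₁² + CV₂²) − 1.96}, with ln(1/0.6) = 0.511

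**1. Reproducing the 80%: two own surveys, MDRI 120 days.**
- KZN: 79.0 recent infections at 4 (CV 0.1135) and 47.5 at 2.4 (CV 0.1463). Difference scale: 0.016/0.00574 = 2.79, power 80%. Log scale: 0.511/0.185 = 2.76, power 79%.
- GP: 77.9 (CV 0.1143) and 46.8 (CV 0.1474), power 79% and 78%.
- Over 118–122 days both provinces give 78–80%. A plain two-proportion test on the recently infected fraction gives 79–81%, needing 7,769–8,035 (KZN) and 10,380–10,734 (GP) per survey.

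**2. Could the 80% be one survey against a known constant?** Scale the article's own 12% CV to the lower incidence: 0.12/√0.6 = 0.155. Difference scale: 0.016/(0.024 × 0.155) = 4.30, power 99%. Log scale: 0.511/0.155 = 3.30, power 91%. So it could not.

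**3. Variance of the external baselines.**
- HIPSS log standard errors: ln(6.52/3.29)/3.92 = 0.174 and ln(5.85/2.74)/3.92 = 0.193. Equal-weight pool: (4.63 + 4.00)/2 = 4.315. Its standard error is √[(4.63 × 0.174)² + (4.00 × 0.193)²]/2 = 0.56, so the CV is 0.13.
- National: (3.04 − 2.04)/3.92 = 0.255, and 0.255/2.54 gives a CV of 0.10.

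**4. The planned comparison: one survey, external baseline, 40% reduction.** Worked case, KZN against pooled HIPSS at MDRI 130 days: I₂ = 2.589, 55.5 recent infections, CV 0.135. Difference scale: 0.01726/0.00660 = 2.615, power 74%. Log scale: 0.511/0.1874 = 2.73, power 78%.

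| Comparison | Baseline CV | Power, MDRI 118–130, DEFF 1 |
|---|---|---|
| KZN, baseline 4 or 4.315, pooled HIPSS CV | 13% | 72–78% |
| GP, national 2.54 | 10% | 77–84% |
| GP, 3 per 100 person-years, national CV borrowed | 10% | 81–86% |
| GP, 3 per 100 person-years, CV assumed (MDRI 130 only) | 20% | 45–55% |

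With DEFF 1.5 at MDRI 130, KZN falls to 66–69% and GP (CV 10%) to 67–79%. With the article's own 12% CV, scaled as in step 2, KZN is 71–73%. On that basis a baseline CV of about 10–11% is the largest that keeps 80% power.

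**5. Matching population.**
- Ages 15–24 in both KZN districts, assuming a flat age distribution: 8,000 × 10/13 ≈ 6,154. The survey CV rises by √(8,000/6,154) = 1.14, from 0.135 to 0.154 at MDRI 130 (0.142 to 0.162 at 118), and power is about 69–72%.
- uMgungundlovu only, ages 15–24 (sensitivity figure): 8,000 × 150/450 × 10/13 ≈ 2,051. At MDRI 130 and prevalence 25% to 15%, 14–16 recent infections are expected, and power is about 40–44% (log) or 49–52% (difference).

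**6. Interval around an observed 40% reduction**, log scale, MDRI 130. KZN against pooled HIPSS: 1 − 0.6·exp(±1.96 × 0.187), or 13% to 58%. The uMgungundlovu contrast at prevalence 25%: 1 − 0.6·exp(±1.96 × 0.297), or −7% to 66%.

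**The case against.** The strongest reply is that the shortfall is modest and that the authors are open about the design. Several parts of it stand.

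- A reader might infer that neither province has 80% power. The figures do not show that. With a baseline CV of 10%, GP is at or near 80%, and ignoring baseline error altogether would push nominal power up, not down.
- A reader might infer that power is only about half of what is claimed. That holds for an uMgungundlovu 15–24 contrast, which the article never names as primary. It powers by province, and the KZN starting rate of 4 per 100 person-years cites the same source as the HIPSS figures. The mismatch of district and age is mainly a question of bias.
- A reader might infer that HIPSS is the only baseline cited for any study district. The sample size section cites a source for the 3 per 100 person-years in the two GP districts, and the study aim offers the national estimate. Neither can be checked further here.
- The Discussion discloses the estimated baseline and the missing comparison arm, and the analysis section confines itself to 40% at two years, so the year-one clause may simply repeat the programme's target.

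What the reply does not reach is the stated power. Disclosing a limitation in the Discussion does not correct a number calculated for another design. Nor is this a detail left to an analysis plan, since the article itself gives the figure.

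**Conclusion.** The concern holds in this form: the 80% is a figure for two surveys of 8,000 in KZN and two of 10,500 in GP, and it does not apply to one survey set against an estimated external baseline.

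For KZN the pooled HIPSS interval gives about 72–78%, or 66–69% at a design effect of 1.5 and MDRI 130. For GP power is undetermined, because the baseline of 3 per 100 person-years comes without an interval; about 77–86% follows if the national CV of 10% is borrowed. All of this rests on the assumed MDRI and design effect. Across MDRI 118–161 days and design effect 1–2, even the two-survey power runs from about 48% to 90%, so the wording of the sample size section and the article's own 12% CV identify the intended design more firmly than the match to 80% alone.

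The 40–50% for uMgungundlovu at ages 15–24 is a sensitivity figure and not the power of the trial. It does not support making that subgroup primary or dropping change estimates in the other three districts, which would alter the primary objective.

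**What to change.** 1. Restate the power by province for one survey against a named external baseline. Include that baseline's published variance, and state the assumed MDRI and design effect. For GP, give the interval of the source behind the 3 per 100 person-years, or show a range.
2. Carry the same variance into the confidence interval of the reduction.
3. Where the baseline covers ages 15–24, compare the same ages in the survey, and flag that HIPSS does not cover eThekwini. Report the matched uMgungundlovu contrast as a sensitivity analysis.
4. Remove the wording that implies more than one survey from the sample size and sampling sections.
5. Mark the year-one 25% reduction in the primary hypothesis as not assessable by this survey.
6. Judge whether 40% was achieved from the confidence interval of the reduction, not from the point estimate or a test of no change.

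The cost is some rewording and a less favourable stated power in KZN (about 69–72% if the comparison is limited to ages 15–24 with a flat age distribution). No extra participants are needed.
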